### Measurements

Data are collected by questionnaire at each of the three measurement points. The main outcome PA was operationalised by the Global Physical Activity Questionnaire (GPAQ) [30, 31]. GPAQ measures prevalence of physical inactivity as well as frequency per week and duration of PA differentiated in three domains, respectively life areas: work (paid and unpaid), transport (e.g., walking and cycling to get to and from places) and leisure time. For each domain, PA conducted for at least 10 minutes continuously during a usual week is assessed. Thereby, work and leisure time PA is measured intensity-specific, which allows to distinguish information on vigorous and moderate PA. Concurrent validity of GPAQ was assessed by comparison with International Physical Activity Questionnaire (IPAQ), a previously validated and accepted measure of physical activity. Thereby, GPAQ showed a moderate to strong positive relationship (concurrent validity: Spearman’s rho 0.45 – 0.65). Reliability was of moderate to substantial strength (kappa 0.67 to 0.73; Spearman’s rho 0.67 to 0.81) [31].

Additionally, a subgroup of 20 patients will receive an accelerometer for the measurement of objective PA at T2 (6 months follow-up). Objective PA will be measured through ActiGraph GT3X tri-axial accelerometers. Participants will be instructed to wear the monitor on a belt around their waist for seven days except during sleeping, showering or swimming. We offer financial incentives to complete questionnaires or to wear accelerometers. Table 2 gives a summary of all measures that will be collected.

**Table 2 Tab2:** **Summary of measures**

	Instrument	Time of measurement^1^
**Primary outcome measure**		
Physical Activity	GPAQ [30, 31]	T1, T2, T3
	Actigraph	T2 (20 persons)
**Secondary outcome measures**		
Subjective prognosis of employment	SPE-Scale [32]	T1, T2, T3
Participation	IMET [33]	T1, T2, T3
**Person-related variables**		
Age, sex, height, weight,	Unstandardized questionnaire	T1
Education level	Unstandardized questionnaire	T1
Health Related Quality of Life	EQ-5D-5 L	T1, T2, T3
**Physical activity related variables**		
Barriers of PA	[34] (modified)	T2, T3
Perceived consequences of PA	[35]	T2, T3
Support of family and friends	Fuchs (modified)	T2, T3
**Indication-specific variables**		
Activities of daily living	FFbH-R [36]	T1, T2, T3
Pain	SF-36, NRS	T1, T2, T3
Disease duration	Unstandardized questionnaire	T1
Complications	Unstandardized questionnaire	T2, T3
Healthcare utilization	Unstandardized questionnaire	T2, T3
**Work-related variables**		
Period of sick listing	Unstandardized questionnaire	T1, T2, T3
Subjective workability	Unstandardized questionnaire	T1, T2, T3
Pension claim	Unstandardized questionnaire	T1, T2, T3

^1^T1 = start of inpatient rehabilitation; T2 = six months follow-up; T3 = twelve months follow-up.

### Sample size

The power calculation is based on the main hypothesis (hypothesis 1). Therefore it is assumed that the intervention group *(Movement Coaching)* shows 90 min per week more PA than the control group. The assumption is based on the estimation of a baseline PA level of 60 min per week in average. On the one hand, an increase of 90 min per week is considered realistic from a practical point of view, on the other hand it is considered a relevant effect as the achieved 150 min per week (assumption: baseline PA = 60 min per week + increase by Movement Coaching = 90 min per week) would go in line with the WHO recommendations on PA [15]. In this current RCT study, 264 participants (132 per group) were calculated to be necessary to detect the assumed relevant difference of 90 min moderate PA per week (~360 MET-min) between the two groups at a two-sided significance level of 0.05 (power 0.8). Anticipating on maximum loss to follow-up of 35% and using a non-parametric statistic test (+5%) the calculated target sample size is 370 patients.

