## Discussion

Low levels of PA in the population require treatment strategies in PA promotion. Therefore, there is a need to develop, evaluate and disseminate approaches that are effective in promoting PA and especially promoting the maintenance of PA. Furthermore, from a Public Health perspective, it is of utmost importance to reach a relevant target group for PA promotion.

Although the study is well-considered, several operational challenges have to be taken into account. One challenge is the recruitment of a sufficient number of patients. During the one-year recruitment, 412 patients could be included in the study. However, recruitment period had to be extended for three months to achieve the target sample size. Second, a selection bias needs to be controlled. Furthermore, the patients’ utilization of the interactive web 2.0 platform as well as target group specific development of the web content seems to be challenging. While planning the study, it is hard to anticipate how to design a motivating web 2.0 platform for CLBP patients after inpatient rehabilitation.

There are several strengths in the design of this study. First, the primary outcome measurement PA will not only be measured subjectively (questionnaires) but also objectively in a subgroup of patients. Second, as far as the authors know, the combination of face-to-face, telephone and internet intervention is new and user experiences of different stakeholders (e.g., patients, providers) can be used in order to improve each approach and/or improve the detailed concept of the comprehensive approach to reach the target group. Third, the 12-month follow-up will result in data about long-term effectiveness of PA promotion in CLBP patients. Furthermore, the examination of associations of PA, subjective prognosis of employment and participation is a promising approach to examine the relative significance of PA in regard of the rehabilitation’s primary objectives according to the ICF model.

CLBP patients seem to be a relevant target group for PA promotion. Based on the results of the current study, modification of Movement Coaching for further indications and target groups is planned.

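### The planned target of 370 adds the 35% loss instead of dividing by 0.65, so at the plan's own maximum loss it gives about 74–76% power, not 80%; the 412 enrolled largely make this up

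*Protocol article*

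**What the plan says.** The Sample size section of the protocol article builds its target in two steps. It first gives the number needed for analysis: "264 participants (132 per group) were calculated to be necessary to detect the assumed relevant difference of 90 min moderate PA per week", "at a two-sided significance level of 0.05 (power 0.8"). It then inflates for attrition and for the choice of test: "Anticipating on maximum loss to follow-up of 35% and using a non-parametric statistic test (+5%) the calculated target sample size is 370 patients". The inflation formula is not printed, and no standard deviation is given.

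The Statistical analysis section confirms that the groups are compared with a Mann-Whitney U test at six and twelve months and that the per-protocol analysis is primary. The Discussion reports the number actually enrolled: "During the one-year recruitment, 412 patients could be included in the study".

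**The concern.** If a fraction L of enrolled patients is lost, N enrolled leaves N × (1 − L) for analysis. To keep a required number, that number must be divided by (1 − L). Multiplying it by (1 + L) always gives too few, and at L = 0.35 the difference is large: the factor is 1.35 where 1 / 0.65 = 1.54 is needed. The target looked as if it had been obtained by adding percentages.

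At stake is whether the paragraph that justifies the trial's power for its main hypothesis is true. It presents 370 as the number that protects 80% power at 35% loss, and later reports of the trial would be expected to rest on it.

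**Working it through.** **Inputs, all from the Sample size section unless noted**
- Evaluable number: 264 (132 per group)
- Two-sided alpha 0.05, power 0.80
- Difference: 90 min per week (about 360 MET-min per week)
- Maximum loss to follow-up: 35%
- Allowance for the rank test: +5%
- Target: 370
- Enrolled: 412 (Discussion)

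**Step 1. Reproduce 370**
- 264 × (1 + 0.35 + 0.05) = 264 × 1.40 = 369.6, rounded up to 370: exact match
- 264 × 1.35 × 1.05 = 374.2 → 375: close, but it makes the same mistake
- 264 × 1.35 = 356.4 → 357: no match
- 264 / 0.65 = 406.2 → 407: no match
- 264 × 1.05 / 0.65 = 426.5 → 427: no match
- 264 / (0.65 × 0.95) = 427.5 → 428: no match
- 264 / 0.60 = 440: no match

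No route that divides by 0.65 comes near 370.

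**Step 2. Patients left at 35% loss**
- Required for analysis: 264, or 264 × 1.05 = 277.2 with the allowance
- From 370: 370 × 0.65 = 240.5
- From 412: 412 × 0.65 = 267.8

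**Step 3. Implied effect size**

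With no SD given, I take 264 as correct and solve backwards (assumption):

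d = (1.960 + 0.842) × √(2/132) = 0.345 by the normal approximation, or 0.346 with the t distribution. This corresponds to an SD of about 260–261 min per week.

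**Step 4. Power at 35% loss**

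Power = Φ(d × √(n/2) − 1.960), where n is the number per group. With the allowance, the completers are first divided by 1.05.

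| Enrolled | Completers | Power without allowance | Completers / 1.05 | Power with allowance |
|---|---|---|---|---|
| 370 | 240.5 | 0.762 | 229.0 | 0.742 |
| 412 | 267.8 | 0.806 | 255.0 | 0.786 |
| 427 | 277.6 | 0.819 | 264.3 | 0.800 |

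Power from the t distribution agrees with these to within 0.001.

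**Step 5. Loss at which 80% power is kept**
- 370: 1 − 264/370 = 28.6% without the allowance; 1 − 277.2/370 = 25.1% with it
- 412: 1 − 264/412 = 35.9% without the allowance; 1 − 277.2/412 = 32.7% with it

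**Step 6. Size of the gap in patients**
- Target: 427 − 370 = 57 (58 for equal arms)
- Enrolled: 427 − 412 = 15 (16 for equal arms)

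**The case against.** Several points can fairly be made on the other side.

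- **The formula is inferred.** This is true, but the conclusion does not need it. However 370 was reached, 65% of it is 240.5, which is below the 264 that the same paragraph calls necessary.
- **The 35% is a maximum, not an expectation.** This stands as a qualification: with smaller losses, 370 would do. But the target is presented as covering that maximum, and it covers only about 25% (29% without the allowance).
- **The trial recruited 412, not 370.** This is the strongest point. A reader might infer that the trial as run misses its 80% power. The document does not support that. At the full 35% loss, 412 leaves about 268 patients, more than 264. It falls below 80% only if the 5% allowance is charged, and then by about 1.4 points.
- **The 5% may not apply.** It is close to the efficiency loss of a rank test under normality (π/3 = 1.047). With skewed activity data the Mann-Whitney test can be more efficient than the t-test. The small gap at 412 rests entirely on this allowance; the gap at 370 remains with or without it.

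A reader might also infer that the per-protocol primary analysis pushes power down by some definite further amount. The direction is right, since the inflation covers only loss to follow-up. However, the article gives no exclusion rate, and the definition of the per-protocol set may be left to the full protocol, so no figure can be attached.

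**Conclusion.** The error in the planned target is real. The stated inputs (264 evaluable, 35% loss, 5% for the rank test) and the stated target of 370 cannot all hold with 80% power. At the planned maximum loss the target gives about 74% power with the allowance and 76% without it, a shortfall of about 4 to 6 points.

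These power figures assume that 264 is correct, that the 5% multiplies the evaluable number, and that the arms are equal. The shortfall in patients needs none of the effect-size assumption.

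Severity is minor to moderate. Recruitment is complete, and enrolment beyond the target restores power at 35% loss to about 79–81%, before any per-protocol exclusions.

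**What to change.** Keep 370 on record as the target used, and add a short correction to the sample size paragraph that:

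1. prints the formula and states that the given inputs require 264 × 1.05 / 0.65 = 427 patients, or 428 for equal arms;
2. states that 370 gives about 74–76% power at 35% loss, the lower figure including the 5% allowance;
3. states that the 412 enrolled leave about 268 patients with follow-up data at 35% loss and give about 79% power with the allowance and 81% without it;
4. says that these figures come before any per-protocol exclusions, and that they take 264 as correct because no SD is reported.

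The cost is one paragraph. No further enrolment and no change of analysis is needed. The downside is that the stated power becomes slightly less favourable.

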**Internet based aftercare**	
Web 2.0 platform (until 12 months after inpatient rehabilitation)	Target group specific information on PA and LBP
	Communication platform

Face-to-face contact of *Movement Coaching* is conducted two times during the three week inpatient rehabilitation (week 2 & week 3). Maximum group size is eight persons and duration of the session is 60 minutes each.

Telephone aftercare comprises at least two calls of the Movement-Coach (week 8 & week 12 after rehabilitation). If the patient requests, further telephone coaching sessions are possible so that call frequency is flexible and can be tailored to the needs of the participant. Furthermore, patients can contact the Movement-Coach by telephone or internet. Main objective of telephone aftercare is to support the patient in his/her PA behaviour. If patients cannot be reached by telephone in the designated week, the Movement-Coach tries to contact him/her within the next two weeks. If a patient cannot be reached within the period of three weeks, the phone coaching is deleted without replacement. The telephone coaching is conducted on basis of a guideline and is scheduled for about 10 minutes. Duration may vary according to the individual needs of patients. All telephone coaching sessions are documented.

Additionally to telephone aftercare, patients have the possibility to use an interactive online platform until 12 months after inpatient rehabilitation. On this platform, patients receive further information on PA and LBP and have the possibility to communicate with the Movement-Coach or other patients.

Two Movement-Coaches were involved in conducting the intervention. Both have a Master’s degree in Sport Science with the main field of study in “Rehabilitation and Health Management”.

The control group receives two lectures on health-enhancing PA during inpatient rehabilitation, 30 minutes each. During the aftercare period, the patients have the possibility to download the lectures from a website. Contrary to the *Movement Coaching* intervention group, after inpatient rehabilitation no communication or interaction between coach and patient or the patients themselves is supported.

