### Statistical analysis

Descriptive statistics will be used to describe the main characteristics of the study population.

The primary analysis will be performed according to the per protocol principle. In addition, an intention-to-treat analysis will be performed. Differences between the intervention group (Movement Coaching) and the control group will be evaluated by Mann-Whithney-U Test at six month (T2) and twelve month follow-up. For all analyses, a two-tailed significance level of p <0.05 is considered to be statistically significant. All analyses will be carried out with IBM SPSS Statistics 21.0.

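### The stated power of 0.8 is not supported for the per-protocol primary analysis: the step from 264 to 370 has no term for per-protocol exclusions

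*Protocol article*

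**What the plan says.** The Sample size section gives the starting number: "264 participants (132 per group) were calculated to be necessary". The design values behind it are a difference of about 360 MET-min per week, a two-sided alpha of 0.05 and power 0.8. Two reasons for enlarging this number follow: "Anticipating on maximum loss to follow-up of 35% and using a non-parametric statistic test (+5%) the calculated target sample size is 370 patients".

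The Statistical analysis section fixes the analysis set: "The primary analysis will be performed according to the per protocol principle". An intention-to-treat analysis is added, and the groups are compared by Mann-Whitney U test at six and twelve months.

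The Intervention section gives the coaching arm two group sessions and at least two telephone calls. For calls that do not succeed it says: "If a patient cannot be reached within the period of three weeks, the phone coaching is deleted without replacement". The control arm has two lectures. The Discussion reports that 412 patients were included.

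**The concern.** A per-protocol set is normally smaller than the set of patients who return the follow-up questionnaire. A patient can complete the questionnaire and still be excluded because the intervention was not received as planned. Loss to follow-up does not count such a patient, and loss to follow-up is the only kind of attrition for which the target allows.

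The power statement and the choice of primary analysis set therefore do not fit together. The practical risk is in interpretation: a non-significant per-protocol result would be read against a power of 0.8 that the calculation does not establish for that set.

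**Working it through.** **Inputs from the Sample size section:** two-sided alpha 0.05; power 0.80; difference 360 MET-min per week; 132 per group (264 in total); maximum loss 35%; rank-test allowance +5%; target 370. From the Discussion: 412 recruited. **Assumed, because the article gives no figure:** per-protocol exclusions of 5–20% of followed-up patients, equal in both arms, with the effect unchanged at 360 MET-min.

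**1. Reproducing the target.** 264 × (1 + 0.35 + 0.05) = 264 × 1.40 = 369.6, which rounds up to 370. The two named allowances account for the whole increase. For comparison, dividing by the retained fraction gives 264 / 0.65 = 406.2, or 264 × 1.05 / 0.65 = 426.5. Neither gives 370.

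**2. Scale for the power figures.** The article states no standard deviation, so one is back-solved from 132 per group: SD = 360 × √(132/2) / (1.960 + 0.842) ≈ 1,044 MET-min per week, a standardised difference of about 0.345. For n analysed patients in equal arms, power is then Φ(2.802 × √(n/264) − 1.960). The plan's rank-test cost is applied by replacing n with n/1.05.

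**3. Before any per-protocol exclusion, at 35% loss.**
- Target: 370 × 0.65 = 240.5; power 0.76 (0.74 with the rank-test cost).
- Recruited: 412 × 0.65 = 267.8; power 0.81 (0.79 with the cost).

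**4. With exclusions, at 35% loss.**

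| Exclusions, both arms | n from 412 | Power | With 5% cost | n from 370 | Power | With 5% cost |
|---|---|---|---|---|---|---|
| 5% | 254.4 | 0.79 | 0.77 | 228.5 | 0.74 | 0.72 |
| 10% | 241.0 | 0.76 | 0.74 | 216.5 | 0.72 | 0.70 |
| 20% | 214.2 | 0.71 | 0.69 | 192.4 | 0.67 | 0.65 |

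**5. How far this depends on the loss.** The exclusions that 412 can absorb before falling to 264 are 1 − 264 / (412 × (1 − loss)). Against 264 × 1.05 = 277.2 the same formula applies.

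| Loss | Tolerated against 264 | Tolerated against 277.2 |
|---|---|---|
| 35% | 1.4% | none |
| 30% | 8.5% | 3.9% |
| 25% | 14.6% | 10.3% |
| 20% | 19.9% | 15.9% |

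At 20% loss and 15% exclusions, 412 leaves 280.2 patients, with power 0.82 (0.80 with the cost).

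**6. How far this depends on the effect.** With 412 recruited, 35% loss and 20% exclusions, power 0.80 returns if the per-protocol effect is 360 × √(264/214.2) ≈ 400 MET-min, about 11% larger (without the rank-test cost). If instead 264 are followed and 20% are excluded from the coaching arm only (105.6 against 132), power is 0.75 at 360 MET-min. It returns to 0.80 at 360 × √[(1/105.6 + 1/132) / (2/132)] ≈ 382 MET-min, about 6% larger.

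**The case against.** The strongest reply is that the shortfall is conditional. The article gives neither a definition of the per-protocol set nor an expected exclusion rate. Such detail is usually left to the full protocol or analysis plan, and exclusions beyond loss to follow-up could be few. The 35% is stated as a maximum, and 412 patients were recruited instead of 370. Removing patients who did not receive the coaching may also raise the mean effect among those who remain, and steps 5 and 6 show that modest changes of either kind restore 0.80. All of this stands, and it rules out a categorical statement that the primary test lacks power 0.8.

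Four further readings are tempting but not supported:

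- *That 0.8 belongs to all followed-up patients.* The article never ties the 264 to a named set. At the target and the maximum loss, the followed-up set has about 240 patients and does not reach 0.8 either.
- *That a missed call removes a patient from the per-protocol set.* The Intervention section only says that the call is dropped. It shows that incomplete delivery was foreseen, not how such patients are classified.
- *That exclusions fall mainly on the coaching arm.* That arm has more components to miss, but no rate is given for either arm.
- *That recruiting 412 leaves no margin.* This is close to true only at the full 35% loss.

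It can also be said that power restated after recruitment changes nothing in the design, and that a confidence interval tells more about a null result. That is fair as to interpretation. It does not justify leaving a published power figure attached to an analysis for which it was not derived.

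**Conclusion.** The point holds as a gap in support for the stated figure, not as proof that the primary test is underpowered. The target is fully explained by two allowances, neither of which concerns per-protocol exclusions, while the primary analysis is per protocol.

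At the plan's maximum loss, power is 0.74–0.76 at the target and 0.79–0.81 with the patients recruited, before any exclusion. Assumed exclusions of 5–20% in both arms bring the recruited sample to 0.79–0.71, or 0.77–0.69 with the rank-test cost. These figures rest on the back-solved standard deviation, equal arms and an effect that stays at 360 MET-min in the per-protocol set. The shortfall shrinks or disappears with smaller loss or a somewhat larger effect among adherent patients.

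**What to change.** In the Sample size section, state which analysis set the 264 and the power of 0.8 refer to. Then restate power for the per-protocol primary set at the planned 360 MET-min effect, starting from the 412 recruited. Either give it over a stated range of loss and exclusions, or use exclusions counted before outcomes are compared; the article says that all telephone sessions are documented, so missed calls can be counted. The observed treatment effect should not enter this figure. If this is not done, the 0.8 should not be attached to the per-protocol result.

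The cost is a short change to the text and a slightly less favourable stated power. No further enrolment or data collection is needed.

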### Statistical analysis

Descriptive statistics will be used to describe the main characteristics of the study population.

The primary analysis will be performed according to the per protocol principle. In addition, an intention-to-treat analysis will be performed. Differences between the intervention group (Movement Coaching) and the control group will be evaluated by Mann-Whithney-U Test at six month (T2) and twelve month follow-up. For all analyses, a two-tailed significance level of p <0.05 is considered to be statistically significant. All analyses will be carried out with IBM SPSS Statistics 21.0.

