Based on the proven health-enhancing effects of PA on LBP and wellbeing, exercise therapy is an integral part of musculoskeletal rehabilitation in LBP patients [16] and therefore widely recommended as a successful therapy for that patient group [13, 17]. Nevertheless, only a few patients integrate health-enhancing physical activity and/or sport activities in their lifestyle. Based on the bio-psycho-social ICF model of functioning, disability and health [18], exercise therapy aims not only at improving body functions but also at improving participation by means of physiotherapy, therapeutic exercise, strengthening exercises, functional task-oriented training and aerobic training [19]. With regard to sustainability of exercise therapy in rehabilitation, its superior aim is to lead patients to an active lifestyle [12, 20]. Athough many studies have shown the effectiveness of exercise therapy in LBP patients, evidence on sustainability is lacking [21]. In consequence, adherence to self-directed exercise and implementing a health-enhancing PA in daily routine after rehabilitation is a common problem for patients [22]. Focussing PA behavior after rehabilitation, there only is evidence on short-term effects. In this context, barriers frequently mentioned are interface problems (e.g. the patients’ not knowing where to train) and lack of patient-oriented knowledge (e.g., being afraid of making mistakes by being physically active). In consequence, support in PA behavior at home is considered to be important [23].

This paper describes the *Movement Coaching* trial, evaluating a multilevel approach promoting PA. The primary research question of this study is:

Does *Movement Coaching* lead to a higher level of PA in chronic LBP patients compared to a control group?

Related to the primary research question, the following hypotheses were developed:The intervention group *(Movement Coaching)* shows 360 MET-min per week more PA than the control group at six months (resp. twelve months) after inpatient rehabilitation.The intervention group *(Movement Coaching)* shows a higher level of leisure time PA than the control group at six months (resp. twelve months) after inpatient rehabilitation.The intervention group *(Movement Coaching)* shows a higher level of transport PA than the control group at six months (resp. twelve months) after inpatient rehabilitation.

Additionally, the following secondary research question is evaluated by an explanatory approach:

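### Per protocol is named as the primary analysis of a superiority trial and intention-to-treat only as an addition, so the headline comparison is not protected by randomisation

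*Protocol article*

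**What the plan says.** The Statistical analysis section fixes the order of the two analyses: "The primary analysis will be performed according to the per protocol principle. In addition, an intention-to-treat analysis will be performed". Nothing elsewhere in the article makes intention-to-treat (ITT) primary, and no reason for the order is given. The groups "will be evaluated by Mann-Whithney-U Test at six month (T2) and twelve month follow-up".

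The Background section states the main hypothesis as superiority: the coaching group "shows 360 MET-min per week more PA than the control group at six months", and likewise at twelve months. The Sample size section uses a two-sided 0.05 level and power 0.8, with 132 patients per group to detect about 360 MET-min per week.

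The Intervention section describes what each arm is offered. According to Table 1 and the text after it, coaching patients have two 60-minute group sessions, at least two calls after discharge (weeks 8 and 12) and a web platform. The opening of the same section counts three face-to-face contacts, which needs reconciling. For calls that fail, "If a patient cannot be reached within the period of three weeks, the phone coaching is deleted without replacement". On the other side, "The control group receives two lectures on health-enhancing PA during inpatient rehabilitation, 30 minutes each", with optional downloads afterwards and no coach contact.

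**The concern.** In a superiority trial, the comparison that randomisation protects is the one between all patients in the arms to which they were assigned. Once patients can be left out because of later behaviour, the two groups may differ for reasons other than the treatment, and the p-value no longer has its nominal meaning. Here that risk attaches to the headline result, because the protected comparison is the additional one.

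Two features make this more than a formality. First, the arms do not have the same amount to comply with, so a compliance-based set could lose different kinds of patient from each. Second, the Background names poor adherence to self-directed exercise after rehabilitation as the problem that the trial addresses. If non-adherent patients were left out, the primary result would describe those who took part, not those who were offered coaching.

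**Working it through.** **Step 1: is there a design reason for per protocol?** The hypotheses ask for more PA than control, the test is two-sided at 0.05, and no margin of non-inferiority or equivalence is stated. The article offers no other reason for the order.

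**Step 2: could exclusions differ by arm?** After discharge, coaching patients have scheduled contacts that can fail; control patients have none. Within the clinic, both arms have two sessions to attend. After discharge, both arms are also asked for the T2 and T3 questionnaires. Unequal exclusion is therefore possible. Whether it happens depends on a definition that the article does not give.

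**Step 3: the outcome SD.** None is stated, so it is back-solved from the plan's own sample size:

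SD = 360 / [(1.960 + 0.842) × √(2/132)] = 360 / 0.345 ≈ 1,044 MET-min per week, taken below as about 1,040.

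Conversely, SD 1,040 with a difference of 360, two-sided 0.05 and power 0.8 returns the plan's 132 per group.

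**Step 4: illustration under no true effect.** Assumptions, none of them from the documents: a share e of the coaching arm, the least adherent, is excluded; no control patient is excluded; adherence and PA have correlation r.

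- Shift of the coaching mean, in SD units = r × φ(z_e) / (1 − e)
- Standard error, in SD units = √[1/(132(1 − e)) + 1/132]
- Rejection rate = P(|Z + shift/SE| > 1.96)

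For e = 0.2, φ(z_e) = 0.280. With r = 0.3 the shift is 0.3 × 0.280 / 0.8 = 0.105 SD, and 0.105 × 1,040 = 109 MET-min. The SE is √(1/105.6 + 1/132) = 0.131, so shift/SE = 0.80 and the rejection rate is 0.127.

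| Excluded, coaching arm only | r | Shift (MET-min) | Share of the 360 target | Two-sided rejection rate |
|---|---|---|---|---|
| any | 0 | 0 | 0% | about 5% |
| 10% | 0.3 | +61 | 17% | 7.5% |
| 20% | 0.3 | +109 | 30% | 12.7% |
| 20% | 0.5 | +182 | 51% | 26.8% |

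**Step 5: the same question with the planned test.** The formulas in Step 4 compare means, whereas the plan uses Mann-Whitney. A simulation with the Mann-Whitney test used 134 per arm (412 × 0.65 / 2, that is, the recruited number less the 35% anticipated loss) and 3,000 runs per scenario:

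- 10% excluded from coaching only, r = 0.3: 7.2%
- 20% excluded from coaching only, r = 0.3: 12.7%
- all coaching-only scenarios with 10% to 30% excluded and r from 0.2 to 0.4: 6.0% to 31.3%
- exclusion unrelated to PA (r = 0): 4.5% to 5.4%
- 20% excluded from both arms with the same selection: 4.6% to 5.3%
- all patients compared as randomised: near 5% throughout

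**The case against.** The strongest objection is that the mechanism is inferred. A reader might conclude that the plan drops unreachable coaching patients, that protocol failure after discharge can occur only under coaching, and that the bias therefore favours coaching. The article does not support any of these as fact:

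- It sets no completion requirement for sessions or calls. It provides for the patient who cannot be reached, so a lapsed call may count as following the protocol.
- Control patients can miss lectures, and patients in either arm can fail to return questionnaires. The Sample size section allows for 35% loss to follow-up and makes no separate allowance for adherence exclusions. That would fit a per-protocol set defined mainly by follow-up completion in both arms, although it does not prove one.
- No relation between reachability and PA is reported. It is plausible that patients who stay in contact are the more active ones, but this is not shown.

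All of this stands, and so the illustration must include its null end: with exclusions unrelated to PA, or equal with the same selection in both arms, the error rate stays near 5%.

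It is also fair to say that ITT is already planned and that CONSORT reporting is promised, so readers should see both results. That softens the consequence but does not remove the defect: if the two analyses disagree, the plan makes the per-protocol result the headline.

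The definition of the per-protocol set may lie in a fuller document, and its absence from the article is not the point here. The order of the analyses is stated outright.

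**Conclusion.** The point holds in this form: the article makes per protocol primary for a superiority question, without a stated reason, and so gives up the protection of randomisation for its headline comparison. This rests on the text alone and needs no assumption about adherence.

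The amount and direction of any bias cannot be taken from the documents. Under the stated assumptions, the type I error ranges from about 5% (no selective or unequal exclusion) through about 13% (20% of the coaching arm excluded, r = 0.3) to about 27% (20% excluded, r = 0.5). The spurious differences run from 0 to 182 MET-min per week against a target of 360. The figures depend on a back-solved SD and on assumed exclusion shares and correlations. All of the non-null scenarios place the exclusions in the coaching arm only.

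**What to change.** Before any unblinded analysis, reverse the order in the Statistical analysis section. Suggested wording: *The primary analysis is by intention-to-treat and compares all randomised patients in the arm to which they were assigned, using the Mann-Whitney U test. The per-protocol analysis is a supportive sensitivity analysis.*

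No patient, visit, measure or test changes, and both analyses are already planned. A longitudinal model or multiple imputation is not part of this change: it would replace or extend the stated test, and the handling of missing outcomes is commonly left to the analysis plan.

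The cost is that the primary estimate may be smaller if non-adherence dilutes the effect. That smaller figure would be the one that answers whether offering coaching works.
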